**Compliance:**

This study will be conducted in compliance with Declaration of Helsinki.

## 2. Background information

Rotavirus is a major cause of morbidity and mortality globally, both in developed and developing countries. There were an estimated 128,500 rotavirus deaths globally in 2016 (1). Almost every child will be infected with rotavirus by the age of 5 years irrespective of where they live, and 35%-40% of diarrheal hospitalizations in this age group are due to rotavirus (2). Besides diarrhoea, rotavirus gastroenteritis is associated with systemic infection, seizures, cognitive deficits, growth faltering, and economic impacts on families. Although it is well recognised that improvements in sanitation and safe water reduce the risk of bacterial and parasitic enteric infections, it is much less understood that clean and safe-water environments are not strongly protective against rotavirus infections. Vaccination is the principal preventive strategy against severe rotavirus infections and the World Health Organization (WHO) recommends that rotavirus vaccine be introduced into all national immunisation programmes (3).

Children in Hong Kong are provided with free vaccinations against 12 antigens in Maternal and Child Health Centres (MCHC) and at school (Primary 1, 5 and 6) under the Hong Kong Government's Childhood Immunisation Programme (CIP). Vaccines not included in the routine CIP schedule, such as rotavirus vaccine, influenza vaccine, and Haemophilus influenzae type b vaccine, can be obtained if parents take their children to doctors working in the private sector. Uptake of rotavirus vaccine was found to be 33.3% in an immunisation survey in preschool children aged 2-5 years conducted by the Department of Health in 2015 (unpublished information obtained from personal communication and from a published study (4)). This uptake rate is much lower than the high immunisation coverage rates of vaccines included in the CIP of over 95% (4;5).

We have previously assessed the disease burden of rotavirus infection in hospitalised children in Hong Kong over 14 rotavirus seasons (1 July 1997 to 31 March 2011) (6). The unadjusted incidence rates per 100,000 person-years based on any International Classification of Disease discharge diagnosis of rotavirus (008.61) were: 249 (0-<1m); 612 (1-<2m); 1066 (2-<6m); 1383 (6-<11m); 959 (1-<2y); 406 (2-<3y); 233 (3-<4y); 124 (4-<5y). This analysis suggested that a discharge diagnosis of rotavirus alone likely under-reported true incidence by a factor of between 1.59-2.02 in children below 5 years of age. Overall we estimated that the cumulative risk of admission with rotavirus infection in Hong Kong children below 5 years was 1 in 33 children.

In 2014/15 we conducted a test-negative case-control study of rotavirus vaccine effectiveness in Hong Kong and showed that the unconditional vaccine effectiveness against hospitalisation for administration of at least one dose of either rotavirus vaccines was 92% (95% confidence interval [CI]: 75%, 98%) (7). The conditional analyses by age only and both age and admission date showed 96% (95% CI: 72%, 100%) and 89% (95% CI: 51%, 97%) protection against rotavirus hospitalisation respectively.

In a Knowledge, Attitudes and Practices study of 500 mother-infant pairs, we showed that family monthly household income had direct effects on both perceived benefits of rotavirus vaccine ( $\beta = 0.16$ ) and self-efficacy to vaccinate the children ( $\beta = 0.16$ ) (8). The highest income quartile were 1.5 times more likely to vaccinate their children with rotavirus vaccine.

In view of the relatively low uptake rate of this safe and effective vaccine, and the very significant disease burden in Hong Kong children, we believe that there is an important research need to assess intervention strategies that could increase rotavirus vaccine uptake in Hong Kong children, particularly in the lower socioeconomic groups. We propose to assess an intervention designed to increase rotavirus vaccine coverage in children by removing financial barriers and increasing mothers' knowledge in rotavirus infection and vaccination.

### **3. Hypotheses and objectives**

#### **Hypotheses:**

1. The uptake of rotavirus vaccine in Hong Kong is associated with socioeconomic status and removal of financial barriers will increase uptake of the vaccine in all socio-economic groups but proportionately more in the low-income groups.
2. The uptake of rotavirus vaccine in Hong Kong is associated with parents' knowledge and attitudes in relation to rotavirus vaccine and infection and providing key information on rotavirus infection and vaccination will increase uptake of the vaccine.

#### **Aims:**

1. To determine whether removal of financial barriers can increase uptake of rotavirus vaccine in children.
2. To determine whether provision of key information on rotavirus infection and vaccination can increase uptake of rotavirus vaccine in children.

### **4. Study design**

This is a prospective, randomised controlled trial (Active control: 2 intervention groups and 1 control group) of two intervention packages designed to increase the uptake of rotavirus vaccine in children.

#### **Subjects**

The following criteria will be used for selection of study participants: (i) postpartum mothers from the study hospitals; (ii) aged older than 18 years; (iii) Cantonese speaking and able to read traditional Chinese; (iv) have a plan to remain in Hong Kong with the infant after delivery for at least 8 months (upper age limit for giving rotavirus vaccine according to product information); (v) no obvious cognitive abnormality; (vi) no serious obstetrical complications and baby is full-term ( $\geq 37$  weeks of gestation) with no congenital abnormalities; and (vii) can provide signed informed consent. Subjects who cannot meet the inclusion criteria would be excluded. A convenience sample of women who meet the inclusion criteria will be invited to participate.

As a token of appreciation, we will offer supermarket coupons with equivalent value of HKD200 (USD26) to subjects on completion of the study by registered mail, in accordance with local experience and international practice. Upon receiving the incentive, participants will be asked to sign on a form of

acknowledgement of receipt. Dates of incentive sent and received and the return of the acknowledgement of receipt will be recorded on a study log sheet as a governance system.

## **Interventions**

### Control Group

Subjects in the control group will receive the publicly available information from the Centre for Health Protection (CHP) about rotavirus infection (<https://www.chp.gov.hk/en/healthtopics/content/24/38.html>) at postnatal wards.

### Intervention Group

There will be two intervention groups. Subjects in both intervention groups will receive the same publicly available information from the CHP about rotavirus infection as the control group. This can ensure all subjects are aware of rotavirus disease and the vaccine. In addition intervention group 1 will receive an intervention package by post one to two days after discharge from hospital, which includes: (i) key information about rotavirus infection and vaccination, and (ii) a hyperlink of a webpage showing clinics in the private sector that provide rotavirus vaccines. A text message reminder for vaccination with the same hyperlink of private clinics will be sent at the children's age of 6 to 8 weeks. Intervention group 2 will receive the same intervention as the intervention group 1, and additionally be given the contact numbers and addresses of a specific community health centre within the United Christian Netherlands Community Health Service (UCN) that will provide rotavirus vaccines free of charge to their infants and in reasonable proximity to their home. A token will be attached in the intervention package to intervention group 2. With the token presented at the health centres, subjects can receive rotavirus vaccine free of charge.

## **Methods**

Mothers will be enrolled in the study at the postnatal wards of two public hospitals (Prince of Wales Hospital and United Christian Hospital). After consent has been obtained and questionnaires have been completed, a study Research Assistant (RA) not involved with other follow-ups will randomly allocate all participants to either control or two intervention groups using block randomisation with 1:1:1 ratio (9). Each group will have 262-263 participants. We will use statistical software R version 3.5.2 to randomly generate the intervention allocation in random block sizes of 6 to 12 with block size kept unknown to investigators and the RA carrying out interviews. This precaution maintains concealment. Once the intervention has been allocated, this RA will not be blinded to participants' group assignment, but the other RA conducting telephone interviews, investigators and participants will be blinded to participants' group allocation. Families in all groups will then be given an envelope containing the standard information about rotavirus infection. The intervention group 1 will receive additional information about rotavirus infection and vaccination and a hyperlink of a webpage showing clinics in the private sector that provide rotavirus vaccines by post one to two days after discharge from hospital and a RA will call and explain the information within a month after the package sent. Then a text message reminder at the children's age of 6 to 8 weeks will be provided. The intervention group 2 will receive the same information as the intervention group 1, and additionally be given information on how to contact a specific UCN health centre where they can receive rotavirus vaccine free of charge and in reasonable proximity to their home.

## **Data collection**

The study data will be collected at two time-points: (i) a face-to-face interview followed by a self-administered questionnaire at enrolment in postnatal wards; and (ii) an online self-administered questionnaire at children's age of approximately 8 months. In the first questionnaire, we will collect information on the key demographic information and mother's knowledge, attitudes and practices in relation to rotavirus vaccine. In the online questionnaire, we will collect the child's rotavirus vaccination history at 8 months old and an electronic copy of the child's vaccination record card. In addition all participants will be asked about the knowledge, attitudes and practices in relation to rotavirus vaccine. Participants will be followed-up by phone if the final questionnaire is not completed.

Knowledge, attitudes and practices of mothers will be assessed by questionnaires based on Health Belief Model (HBM). The HBM is a simple, widely used framework to explain human health decision-making and behaviour (10;11). It was developed in the 1950s and improved in 1980s (12-14). It contains six concepts to predict how humans make decisions. These include perceived susceptibility and severity of illnesses, perceived benefits and barriers of interventions, cues to action and self-efficacy. The questionnaires are based on previous intervention study to increase influenza vaccine uptake (15). The modified questionnaire will be pilot-tested in approximately 30 mothers at the postnatal wards of the two study hospitals so as to ensure the internal consistency of questionnaire items within constructs is acceptable. Questionnaires will then be refined if necessary.

## **5. Selection of subjects**

The provision of publicly available information from the CHP about rotavirus infection to all participants may increase their knowledge of the vaccine in subjects who do not know the vaccine before joining the study. To ensure we will have enough sample to examine the study objectives, we assume the baseline rotavirus vaccine uptake would be 40%. We estimate the intervention 2 will increase the subjects' rotavirus vaccine uptake from 40% to at least 55%. Anticipating 20% drop-out, based on a required power of 80% and a significance level of 0.05, by using G\*Power version 3.1.9.2, the sample size required in each group is 262-263, and 788 in total. 459 and 329 subjects will be recruited in the Prince of Wales Hospital and United Christian Hospital respectively.

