### **Statistical analysis**

To ensure data quality, the data will be double-entered and validated using EpiData. Intention-to-treat analysis will be used with missing status of rotavirus vaccination taken as no vaccination. An initial univariate analysis will be performed on all variables to derive means, standard deviations and ranges. These initial results will be examined for possible errors and corrected as necessary. To assess the usefulness of the interventions, chi-squared tests will be used to compare rotavirus vaccine uptakes between control and intervention groups. To determine whether removal of financial barriers can increase uptake of rotavirus vaccine in children (study objective 1), we will compare intervention group 2 with the intervention group 1. To determine whether provision of key information on rotavirus infection and vaccination can increase uptake of rotavirus vaccine in children (study objective 2), we will compare intervention group 1 with the control group. We will use multiple regression models to assess the association between the rotavirus vaccination uptake rate and mothers' knowledge and attitudes before and after delivering intervention materials. The models will then be compared to assess the factors influenced by the interventions. To determine the change in knowledge and attitudes after receiving intervention information, permutation tests (16) will be performed on the paired data. All statistical analysis will be performed using statistical software R version 3. 5.2 and a two-tailed p-value <0.05 will be taken as statistically significant.

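### The sample size is justified for group 2 against control, but the two aims are tested by group 2 against group 1 and group 1 against control, whose power is not given and would mostly be well below 80%

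*Protocol*

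**What the plan says.** Protocol Section 5 (Selection of subjects) offers its calculation as the assurance that the sample will serve the study objectives. After noting that everyone receives the public rotavirus information, it says "we assume the baseline rotavirus vaccine uptake would be 40" per cent, and then that intervention 2 is expected to raise "rotavirus vaccine uptake from 40% to at least 55" per cent. The other inputs are "Anticipating 20% drop-out" and "based on a required power of 80% and a significance level of 0.05". The result is 262-263 per group and 788 in total.

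Protocol Section 8 (Statistical analysis) assigns a contrast to each aim. For removal of financial barriers, "we will compare intervention group 2 with the intervention group 1". For key information, "we will compare intervention group 1 with the control group". A preceding general sentence provides chi-squared tests of control against the intervention groups. The analysis is by intention to treat with unknown vaccination status counted as unvaccinated, and "a two-tailed p-value <0.05 will be taken as statistically significant".

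Neither section assumes an uptake for group 1. Section 3 expects both information and free vaccine to raise uptake.

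**The concern.** The public information described in Section 5 is all that the control group receives (Section 4, Interventions). The 40% is therefore most naturally the control uptake, and 40% to 55% is the difference between group 2 and control. Group 2 receives the group 1 package plus free vaccine, so the difference tested for aim 2 and the difference tested for aim 1 add up to those 15 points. If both hypotheses are true, each is smaller than 15.

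The trial exists to separate the effect of information from the effect of cost. As sized, the better the information works, the weaker the test of free vaccine. A reader who takes the 80% as applying to the aims could treat a non-significant aim contrast as evidence of no effect when the trial had little chance of detecting a plausible one.

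**Working it through.** **Inputs.** Uptake 40% and 55%, power 80%, alpha 0.05, dropout 20%, 788 in total (Section 5); 1:1:1 allocation (Section 4, Methods), so 788/3 = 262.67 per arm; two-tailed 0.05 and missing counted as unvaccinated (Section 8). Group 1 uptake is not given, so it is varied between 40% and 55% as an assumption. Missingness is assumed to be 20% in every arm and unrelated to vaccination.

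**1. The plan's own figure.** Pooled two-proportion formula, with p̄ the mean of the two proportions:

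n = [z(1−α/2)·√(2p̄(1−p̄)) + z(0.80)·√(p₁(1−p₁)+p₂(1−p₂))]² / (p₂−p₁)²

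- Two-sided 0.05: (1.960·0.7062 + 0.8416·0.6982)² / 0.15² = 172.8, so 173; 173/0.8 = 216.25, so 217 per group (651 in total). With a continuity correction: 186, then 233 per group.
- Two-sided 0.025: (2.2414·0.7062 + 0.8416·0.6982)² / 0.15² = 209.4, so 210; 210/0.8 = 262.5 per group, and 3 × 262.5 = 787.5, so 788.

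The stated number follows from two-sided 0.025, which the protocol does not mention, and not from the stated 0.05. With 210 evaluable per group, 40% against 55% has 87% power at 0.05 and 80% at 0.025.

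**2. Power under the stated analysis.** All 262.67 per arm are analysed, and 20% missing scales each uptake by 0.8, so 40% and 55% become 32% and 44%.

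Power = Φ{[|p₂−p₁|·√n − 1.96·√(2p̄(1−p̄))] / √(p₁(1−p₁)+p₂(1−p₂))}

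- Group 2 against control (32%, 44%): (1.945 − 1.345)/0.681 = 0.88, power 81%.
- Group 1 at 47.5% (38% as analysed), against control: (0.972 − 1.322)/0.673 = −0.52, power 30%.
- Group 2 against group 1 (38%, 44%): (0.972 − 1.363)/0.694 = −0.56, power 29%.

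Each cell below gives group 1 against control / group 2 against group 1, at two-sided 0.05:

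| Group 1 uptake | Stated analysis, 20% missing | 210 evaluable, dropouts excluded | All observed, no dropout |
|---|---|---|---|
| 42.5% | 7% / 65% | 7% / 73% | 8% / 82% |
| 45% | 16% / 46% | 18% / 54% | 21% / 63% |
| 47.5% | 30% / 29% | 34% / 34% | 41% / 40% |
| 50% | 48% / 15% | 54% / 17% | 64% / 21% |
| 52.5% | 66% / 7% | 73% / 7% | 82% / 8% |

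**3. Where 80% is reached.** Under the stated analysis, group 2 against group 1 reaches 80% only if group 1 uptake is below about 40.2%, and group 1 against control only if it is above about 54.8%. With 210 evaluable the limits are about 41.4% and 53.6%. With no dropout they are about 42.8% and 52.2%. On no basis do both contrasts reach 80% together within a 15-point gap.

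**4. What the arms can resolve.** From 32%, 80% power needs about 43.8%, a difference of 11.8 points as analysed, or 11.8/0.8 = about 14.8 points among responders. The 95% half-width for one step is 1.96·√[(0.32·0.68 + 0.38·0.62)/262.67] = 8.1 points.

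**The case against.** The strongest reply is that the shortfall rests on an uptake the protocol never states. A reader might infer that neither aim contrast has 80% power whatever happens. The documents do not support that. If group 1 sits almost at the control level, group 2 against group 1 has about the planned power; if it sits almost at the group 2 level, group 1 against control does. The protocol also says at least 55%, so 55% is a floor, and a large enough total effect would power both steps. What remains is conditional: at the 55% on which the calculation rests, with both hypotheses true by more than a small step, both contrasts fall short.

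A reader might also infer that the powered comparison is absent from the analysis. It is not: the general chi-squared sentence covers group 2 against control, though it ties that comparison to neither aim.

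Section 5 says baseline rather than control. If it meant group 1, aim 1 would be the powered contrast and aim 2 would have no planned effect at all, so the gap would move rather than close.

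Finally, the match to two-sided 0.025 may mean that two comparisons were allowed for. The protocol does not say so. It would not help the aims: at 0.025, with 210 evaluable and group 1 at 47.5%, each has 24% power.

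**Conclusion.** The point holds in conditional form. The stated 80% belongs to group 2 against control, where the protocol's own analysis gives about 81% at two-sided 0.05. It does not carry over to the contrasts that answer the aims. For group 1 uptakes of 45% to 50%, power is about 16% to 48% for information and 46% down to 15% for free vaccine. This assumes that 40% is the control uptake, group 2 reaches 55%, 20% are missing equally in each arm, and missing counts as unvaccinated. Less missingness improves the figures but leaves the midpoint at about 40% for each contrast.

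It would go too far to conclude that the comparisons are invalid. Randomisation, outcome and estimates are unaffected. What is wrong is the power claimed for the objectives, together with an alpha that does not reproduce the sample size.

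**What to change.** In Section 5:

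- Say that the stated power refers to group 2 against control and does not apply to the two aim contrasts.
- State the alpha actually used. The stated 0.05 gives about 217 per group, while 262-263 matches two-sided 0.025. Reconcile this with the 0.05 in Section 8.
- Give the power of group 2 against group 1 and of group 1 against control over a range of group 1 uptakes, under the missing-as-unvaccinated rule, with the detectable difference of about 11.8 points as analysed (about 14.8 among responders).

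In Section 8, keep the aim contrasts as they are and report each as a risk difference with a 95% confidence interval (half-width about 8 points), so that a non-significant result is not taken as no effect. Naming group 2 against control as the primary comparison is optional: it would match the sizing but answers neither aim by itself.

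The cost is protocol wording, with no extra participants. The downside is that the power stated for the two aims becomes less favourable.

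### The 262-263 per group (788 in total) does not follow from the stated 0.05 level, which gives about 217 per group; it reproduces exactly at a two-sided 0.025 that the protocol does not mention

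*Protocol*

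**What the plan says.** Section 5 (Selection of subjects) assumes a baseline uptake of 40%, rising to at least 55% with intervention 2. It adds "Anticipating 20% drop-out", works "based on a required power of 80% and a significance level of 0.05", names G\*Power 3.1.9.2 as the software, and states that "the sample size required in each group is 262-263, and 788 in total". The hospital targets of 459 and 329 sum to the same 788. Section 4 (Methods) repeats the group size and allocates "using block randomisation with 1:1:1 ratio".

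Section 8 (Statistical analysis) names chi-squared tests for uptake and ties each of the two objectives to one comparison: group 2 against group 1, and group 1 against control. It counts a missing vaccination status as not vaccinated, and says that "a two-tailed p-value <0.05 will be taken as statistically significant". Neither section mentions 0.025 or any division of alpha.

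**The concern.** Every input that a two-proportion sample size needs is printed, so the result should be reproducible. It is not, and the gap is too large to be rounding or a choice between standard formulas. The figures match a level half the one stated.

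What is at stake is the decision rule for the primary outcome. If the trial was designed with 0.025 per comparison, a p-value between 0.025 and 0.05 on either objective would not have met the design's criterion, yet it would be declared significant under Section 8. If 0.05 per comparison was intended, the 80% is not the power that this size gives. A reader cannot tell which holds, and the question should be settled before results are seen.

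**Working it through.** **Inputs.** p1 = 0.40, p2 = 0.55, power 80%, alpha 0.05 and drop-out 20% (Section 5); two-tailed chi-squared test (Section 8); three equal groups (Section 4).

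**Formula.** With p̄ = (p1 + p2)/2 = 0.475,

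n = [z(1−α/2)·√(2p̄(1−p̄)) + z(0.80)·√(p1(1−p1) + p2(1−p2))]² / (p2 − p1)²

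The two roots are √0.49875 = 0.7062 and √(0.24 + 0.2475) = 0.6982, and z(0.80) = 0.8416.

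**At the stated two-sided 0.05** (z = 1.960):
- n = (1.3842 + 0.5876)² / 0.0225 = 172.8, so 173 evaluable per group.
- 173/0.8 = 216.25, so 217 per group.
- 3 × 173/0.8 = 648.75, so 649 in total (651 if each group is rounded up first).
- Against the printed total: 788 − 649 = 139, and 139/649 = 21%.

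**Reproducing the printed figure, at two-sided 0.025** (z = 2.241):
- n = (1.5829 + 0.5876)² / 0.0225 = 209.4, so 210 evaluable per group.
- 210/0.8 = 262.5, which accounts for the unusual 262-263.
- 3 × 262.5 = 787.5, so 788.

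**Other routes for 40% against 55% with 80% power:**

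| Route | Evaluable per group | After 20% drop-out |
|---|---|---|
| Two-sided 0.05, unpooled variance | 171 | about 213 |
| Two-sided 0.05, arcsine | 173 | 216 |
| Two-sided 0.05, noncentral chi-squared | 174 | 218 |
| Two-sided 0.05, Fisher exact | about 184 | 230 |
| Two-sided 0.05, continuity-corrected | 186 | 233 |
| One-sided 0.05 | 136 | 170 |
| Two-sided 0.0167 (three-way split) | 231 | 289 |

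Inflating by n × 1.2 instead of dividing by 0.8 gives 208 (pooled) or 224 (continuity-corrected) at two-sided 0.05. None of these gives 262-263.

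**Power that the planned size gives.** Power = Φ{[(p2 − p1)√n − z(1−α/2)·√(2p̄(1−p̄))] / √(p1(1−p1) + p2(1−p2))}.

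*Drop-outs excluded*, n = 210, 40% against 55%; 0.15 × √210 = 2.1737:
- 0.05: (2.1737 − 1.3842)/0.6982 = 1.131, power 87.1%.
- 0.025: (2.1737 − 1.5829)/0.6982 = 0.846, power 80.1%.

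*Missing counted as not vaccinated*, n = 262.5. With 20% missing in each group, the rates become 0.8 × 40% = 32% and 0.8 × 55% = 44%; the roots become √0.4712 = 0.6864 and √0.464 = 0.6812; 0.12 × √262.5 = 1.9442:
- 0.05: (1.9442 − 1.3454)/0.6812 = 0.879, power 81.0%.
- 0.025: (1.9442 − 1.5386)/0.6812 = 0.595, power 72.4%.

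The number needed for 80% power at 0.05 with these diluted rates is (1.3454 + 0.5733)² / 0.0144 = 255.7, so 256 randomised per group.

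**The case against.** The strongest reply is that the size does what Section 5 asks at the level it states. Section 8 keeps every randomised mother and counts missing status as not vaccinated. On that rule 256 per group are needed at 0.05 and 262-263 are planned, within 3%. Power is 81% against a target of 80%. This stands as an answer to any claim of harm, but it does not rescue the derivation. Section 5 applies a drop-out inflation instead of diluted rates, and this route gives 256, not 262.5.

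The match at 0.025 could also be a coincidence. A single three-group chi-squared test on 2 degrees of freedom at 0.05, with a middle-arm uptake between 45% and 50%, gives totals of about 771 to 801, a range that includes 788. But the protocol states no middle-arm rate and describes no such test. That route is no better documented than a split of alpha, and it yields 788 only if the unstated rate is tuned.

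Finally, control of multiplicity is often left to a statistical analysis plan, which is not at hand. That is fair, and a missing adjustment is not the point here. The point is that a printed number disagrees with the inputs printed beside it.

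**Conclusion.** The mismatch is established: 262-263 per group and 788 in total cannot be obtained from 40% against 55%, 80% power, 0.05 and 20% drop-out by any standard two-group method tried. The pooled formula gives about 217 and 649. Two-sided 0.025 reproduces the printed figures exactly.

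Three stronger conclusions are tempting, and the protocol does not support them:

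- **That the trial was designed with a Bonferroni split, so that Section 8 tests at twice the design level.** Two comparisons and an exact match at 0.05/2 make this the likeliest explanation. It remains an inference, since no section says so and Section 5 describes only one contrast.
- **That the trial is 21% too large.** The 139 extra mothers are surplus only if drop-outs are excluded. Under the plan's own rule for missing status, the size is about right at 0.05.
- **That the trial is underpowered.** At 0.05 it is not, for 40% against 55%. Power falls short (72%) only if 0.025 is the intended level and missing status is counted as not vaccinated.

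The power figures assume 20% missing in each group and apply only to the 40% against 55% contrast. Because the number randomised need not change and power is adequate at the stated level, this should be fixed but does not threaten the trial.

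**What to change.** Leave the sample size at 788. In Section 5, state the test and the alpha actually entered in G\*Power and, if the level was divided, over which comparisons. Then make Section 8 agree:

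- **If 0.05 per test is intended:** keep Section 8 and replace the 80% in Section 5 with the power that this size gives for 40% against 55%: about 87% with drop-outs excluded, or about 81% when missing status counts as not vaccinated (32% against 44%).
- **If 0.025 per comparison was intended:** write it into Section 5, use the same level for the two uptake comparisons in Section 8, and state that power is about 80% with drop-outs excluded but about 72% under the missing-as-not-vaccinated rule.

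Only the authors can say which applies. The cost is a sentence or two in each section and a look at the saved sample-size output.
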